### Research Aim and Hypotheses

This study aims to elucidate the effects of improved SQ on executive function. The following hypotheses will be investigated in the trial:

ICBT-I will lead to a significant improvement in SQ compared with the SHE intervention at 1 month (T2), 3 months (T3), and 6 months (T4) postintervention.ICBT-I will lead to a significant improvement in executive functioning compared with the SHE intervention at 1 month (T2), 3 months (T3), and 6 months (T4) postintervention.ICBT-I will lead to a significant improvement in total sleep time (TST), SOL, number of awakenings (NOA), wake time after sleep onset (WASO), and sleep efficiency (SE) compared with the SHE intervention at 1 month (T2), 3 months (T3), and 6 months (T4) postintervention.Dysfunctional beliefs, attitudes about sleep, presleep worry, and sleep hygiene will significantly mediate the between-group differences in study outcomes at 1 month (T2), 3 months (T3), and 6 months (T4) postintervention.

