### Sample Size Estimation

As shown in Figure 3, the sample size for the RCT was calculated using G*Power software (Heinrich-Heine-Universität Düsseldorf), selecting the *F* tests for analysis of variance: repeated measures, within-between interaction. The calculation was based on a precision level of 0.05, a study power of 95%, an effect size of 0.20, and a correlation coefficient of 0.5 among the outcome measures. Therefore, the minimum required sample size for each group is 56. A low effect size of 0.20 was chosen based on previous interventions addressing SQ [33]. After adjusting for a 10% dropout rate, the sample size was increased to 60 medical students per group. Given that this is a 2-arm RCT, a total of 120 medical students will be required to complete the study.

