### Assessment Points

Participants in both groups will be assessed at baseline (week 0 or pretreatment assessment), week 6, 1 month, 3 months, and 6 months after the intervention. T0 represents the pretreatment assessment, while the subsequent 4 assessment points are designated as T1, T2, T3, and T4, respectively.

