### Data Analysis

Data will be analyzed using SPSS version 29 (IBM Corp.). Descriptive statistics will be used to obtain information on dropout rates, recruitment, and completeness. All participants will be included in the intention-to-treat analysis for assessing the main efficacy of the intervention, with no planned interim analysis for efficacy or futility. The baseline characteristics of participants will be presented according to their randomized group, with no inferential statistical tests performed at this stage.

For the RCT design, outcome measures will be assessed for normality and presented as either means with SD or medians with IQR, depending on the data distribution. Participants’ characteristics will be summarized using descriptive statistics, with categorical data presented as frequencies and percentages, and continuous data presented as means (SD) or medians (IQR). Normality will be tested using the Kolmogorov-Smirnov and Shapiro-Wilk tests.

Changes in all outcome measures (ie, SOL, TST, NOA, WASO, SQ, SE, dysfunctional beliefs about sleep, presleep arousal, and SHI) from pretreatment (T0) to the first (T1), second (T2), and third (T3) time points will be assessed for treatment effects using repeated measures analysis of variance. Both treatment and time interaction effects will be examined. Paired samples *t* tests will then be conducted within each condition to evaluate possible simple or main effects. Significant findings and statistical trends will be further analyzed using Cohen *d* effect size, which accounts for the correlation between pre- and posttreatment values.

Potential confounding factors, particularly class year and gender, will be addressed and analyzed as variables that may influence the research outcomes. These factors will be incorporated into the analysis through both univariate and multivariate linear regression analyses, allowing for the isolation of each factor and its association with the outcomes of interest.

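### The hypotheses claim superiority at T2, T3 and T4, but no test named in Data Analysis compares the arms at those visits, and T4 is not in the model

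*Protocol article*

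**What the plan says.** **Hypotheses (Research Aim and Hypotheses).** The first reads "ICBT-I will lead to a significant improvement in SQ compared with the SHE intervention at 1 month (T2), 3 months (T3), and 6 months (T4)". The second (executive functioning) and third (sleep parameters) name the same three visits. T1, the end-of-treatment assessment, is not claimed.

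**Schedule (Assessment Points).** "T0 represents the pretreatment assessment, while the subsequent 4 assessment points are designated as T1, T2, T3, and T4, respectively". There are five occasions in all.

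**Efficacy analysis (Data Analysis).** The changes to be analysed run "from pretreatment (T0) to the first (T1), second (T2), and third (T3) time points", so T4 is not listed. As to method, the section states that these changes "will be assessed for treatment effects using repeated measures analysis of variance. Both treatment and time interaction effects will be examined". The outcomes spelled out for this model are the sleep parameters, sleep quality, dysfunctional beliefs, presleep arousal and the Sleep Hygiene Index. Executive function is not among them.

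**Follow-up tests (Data Analysis).** "Paired samples *t* tests will then be conducted within each condition to evaluate possible simple or main effects". The section also names Cohen d using the pre-post correlation, regressions on class year and gender, and mediation models for hypothesis 4. None of these is described as a comparison of the arms at a visit.

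**Sample size (Sample Size Estimation).** The calculation uses G*Power with "analysis of variance: repeated measures, within-between interaction".

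**Abstract, Methods.** The primary outcome is put more loosely, as between-group differences after baseline. That wording could take in T1.

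**The concern.** Each efficacy hypothesis is about the difference between arms at a named later visit. The null hypothesis of the interaction test is that the two arms run parallel over all occasions in the model. Rejecting it shows neither the visit at which the arms differ nor which arm is ahead. A benefit present when treatment ends and gone a month later can produce a significant interaction, and that result could then be reported as support for hypotheses of lasting benefit.

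The other named tests do not close the gap. The treatment main effect averages T0, where randomisation makes the expected difference zero, with T1, which no hypothesis claims. Paired t tests within each arm show change from baseline; improvement in one arm, or in both, is not evidence that one arm is better. As written, the 6-month claim has no test in this model, and hypothesis 2 is not visibly covered.

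**Working it through.** **Inputs.** From the protocol: 60 per arm, correlation 0.5 and alpha 0.05 (Sample Size Estimation); occasions T0 to T3 (Data Analysis). Assumed here: between-arm differences of 0.3, 0.4 and 0.5 SD, equal variances, compound symmetry and no dropout. The protocol gives no SD-unit difference by visit.

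**The plan's own figure.** I took the effect size 0.20 as Cohen f and used the G*Power default noncentrality f²·N·m/(1−ρ). With m = 4 occasions, N = 56 gives 0.04 × 56 × 4 / 0.5 = 17.92 and power 95.4%. The stated 56 is therefore matched as a total, not per group. The protocol text does not state the number of occasions, and the G*Power figure is not shown. This is a separate matter on which the present point does not depend.

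**Interaction test.** For between-arm differences d_t in SD units, the noncentrality is (n/2)·Σ(d_t − d̄)²/(1−ρ), with 3 and 2 × 59 × 3 = 354 degrees of freedom.

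- T1-only profile (0, d, 0, 0): d̄ = d/4, and Σ(d_t − d̄)² = (3d/4)² + 3(d/4)² = 0.75d².
- Sustained profile (0, d, d, d): d̄ = 3d/4, and Σ(d_t − d̄)² = (3d/4)² + 3(d/4)² = 0.75d².

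The two sums are identical, so the power is identical:

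| d (SD, assumed) | Noncentrality 30 × 0.75d²/0.5 | Power, T1-only | Power, sustained T1–T3 |
|---|---|---|---|
| 0.3 | 4.05 | 36% | 36% |
| 0.4 | 7.20 | 60% | 60% |
| 0.5 | 11.25 | 81% | 81% |

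Adding T4 leaves the two profiles equal, at 34%, 58% and 80%. Simulation at 0.5 SD (8,000 trials) agrees: 81% for T1-only over T0–T3, and 80% for each profile over T0–T4.

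**Treatment main effect.** A sustained difference of 0.5 SD at T1 to T3 enters as (0 + 0.5 + 0.5 + 0.5)/4 = 0.375. A T1-only difference of 0.5 SD enters as 0.125. The effect mixes T0 and T1 with T2 and T3, so it isolates none of the hypothesised visits.

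**Between-arm contrasts at T2, T3 and T4.** The baseline-adjusted difference at one visit has residual variance 1 − 0.5² = 0.75 and standard error √(2 × 0.75/60) = 0.158. By simulation, with two-sided 0.05 at each visit:

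- Sustained difference at T1 to T4: all three visits are significant in roughly 18%, 43% and 71% of trials at 0.3, 0.4 and 0.5 SD.
- T1-only difference of 0.5 SD: all three are significant in well under 1% of trials, and at least one in about 13%. The 13% is the ordinary chance rate for three unadjusted tests.

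**Average of T2 to T4 as a single test.** With a difference of 0.5 SD at T2 only, it rejects in about 28 to 30% of trials, although the T3 and T4 claims are then false.

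**The case against.** **Data Analysis names no single decisive test.** This stands. It says that both treatment and interaction effects will be examined, and only the sample size section points to the interaction. A reader might infer that the interaction is the declared success criterion; the text does not go that far. The point does not need it, because none of the named tests addresses the hypothesised visits.

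**The wording about changes from T0 to T1, T2 and T3 could mean separate two-occasion analyses.** In a T0-versus-T2 analysis the interaction is exactly the between-arm difference in change at T2. That reading is possible, and under it T2 and T3 would be covered. The protocol does not say so, the only follow-ups it names are within-arm, and T4 would still have no test.

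**This is detail for the analysis plan.** It would be if the article were silent. The article fixes the model, its occasions and its follow-up tests, and the follow-up it fixes cannot answer the hypotheses.

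**The abstract's primary outcome could include T1.** This stands as an inconsistency with the hypotheses, and the protocol needs to settle it.

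**A reader might infer that the interaction wastes power against a lasting benefit.** That holds only against a one-degree-of-freedom test of averaged visits. Against the claim as written, superiority at all three visits, the targeted requirement has less power than the interaction (71% against 81% at 0.5 SD). If 0.20 is read as Cohen f over four occasions, 0.75d² = 4 × 4 × 0.04 = 0.64, so d is about 0.92 SD, and the interaction and averaged tests both have power close to 100%. Loss of power is therefore not part of this point.

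**Conclusion.** The point holds in this form: the hypotheses name T2, T3 and T4, and no named efficacy test is a between-arm comparison at those visits. The equality of the interaction's power for a T1-only and a sustained difference is exact under compound symmetry. Its level, about 36%, 60% and 81%, rests on assumed differences of 0.3, 0.4 and 0.5 SD, 60 per arm, correlation 0.5 and no dropout. A T1-only effect can trigger rejection; whether it does depends on its size. The absence of T4 from the model and of executive function from its outcome list widens the gap.

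The documents do not support two stronger readings: that the interaction is the sole declared test, or that the plan is generally underpowered for a sustained benefit. This should be corrected before analysis.

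**What to change.** In Data Analysis:

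1. Include T4 and executive function in the repeated-measures model.
2. Base the conclusions for hypotheses 1 to 3 on the baseline-adjusted ICBT-I minus ISHE difference at each of T2, T3 and T4, with 95% confidence intervals. State whether support for a hypothesis requires all three visits. If any one visit were to suffice, the three tests would need multiplicity control, given the 13% chance rate above.
3. Report the omnibus interaction, the T1 difference and the within-arm changes as descriptive.
4. If an average over T2 to T4 is given, label it a summary of overall post-treatment benefit, not evidence of superiority at each visit.
5. Align the abstract's primary outcome wording with the visits in the hypotheses.

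The cost is about one paragraph plus the abstract wording. T4 is already scheduled, and the Results section places analysis after T3 and T4 collection, so no new data are needed. There are two downsides: a T1-only effect no longer counts as success, and requiring all three visits has less power than the omnibus test (about 71% against 81% at an assumed 0.5 SD).

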### Randomization and Allocation Concealment

As participants will be recruited from 2 different universities, a stratified randomization method will be used to ensure balance between the groups from each university. Eligible students will be grouped by university and gender before random selection. Gender will serve as a matching factor during the stratified randomization process to ensure a comparable number of female and male students are recruited from both universities.

Data will be collected from volunteer medical students, and the researchers will have no influence on the randomization process or access to future allocations. Each participant will be assigned an identification number and listed before being randomized into either the ISHE or ICBT-I group using online randomization software [34]. A total of 60 students will be allocated to each group.

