### Assessment of Participants’ Safety

The risk of severe or serious adverse events in this study is low, as no such events have been reported in previous studies using CBT-I for the management of insomnia [49].

Nevertheless, studies have shown that sleep restriction therapy, one of the components of CBT-I, may increase levels of vigilance impairment and daytime sleepiness among participants, potentially leading to adverse situations such as suicide attempts, incidents, and formal complaints about the online intervention [49]. As both the intervention and assessment will be conducted online, the researcher may not be made aware of all such events. The researcher will, however, instruct participants to complete a feedback form to report any self-reported adverse effects [50].

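### The planned repeated measures ANOVA conventionally drops anyone with a missed visit, which does not fit the promise to analyse all participants; it also omits the randomisation strata and baseline adjustment, at a cost in precision only

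*Protocol article*

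**What the plan says.** In Data Analysis, the protocol article states the analysis population: "All participants will be included in the intention-to-treat analysis for assessing the main efficacy of the intervention". Two paragraphs later it gives the efficacy method. It takes the change in each outcome "from pretreatment (T0) to the first (T1), second (T2), and third (T3) time points" and says that these changes "will be assessed for treatment effects using repeated measures analysis of variance", with treatment and time interaction effects examined, followed by paired t tests within each arm. The software is SPSS version 29. No imputation or likelihood-based method is mentioned. Sample Size Estimation allows for 10% dropout and assumes a correlation of 0.5 among the outcome measures.

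On strata, Randomization and Allocation Concealment says that "a stratified randomization method will be used to ensure balance between the groups from each university", and that students are grouped by university and gender. On covariates, Data Analysis says: "Potential confounding factors, particularly class year and gender, will be addressed and analyzed". This is to be done through univariate and multivariate linear regressions that are described separately from the ANOVA. University is not named anywhere in the analysis.

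**The concern.** The section fixes both a population and a method, and the two do not fit. Repeated measures ANOVA as SPSS conventionally runs it needs a full row per participant, so one missed visit removes the person and every value already collected. With dropout expected, the main result would rest on completers, although the text says all participants are included.

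This matters most if dropout differs by arm. Sleep restriction is given in the ICBT-I arm only (Table 1 and the section on internet-based SHE). Assessment of Participants' Safety says that it "may increase levels of vigilance impairment and daytime sleepiness among participants". Dropout related to arm and to response is therefore plausible, though the protocol does not predict it.

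Two further features cost precision. The factors used to stratify randomisation are not in the efficacy model. Baseline enters only as a repeated level or as the origin of the change, not as a covariate.

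**Working it through.** **1. Loss at the protocol's own dropout figure.** Inputs: 120 randomised (60 per group) and 10% dropout, both from Sample Size Estimation. Excluded: 120 × 0.10 = 12. Remaining: 108, or 54 per group. This is the only loss figure that rests on the protocol's own numbers.

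**2. Loss if visits are missed independently (assumed rates).** The ANOVA as written covers three follow-ups, T1 to T3.
- 5% missed per visit: 0.95³ = 0.857, and 120 × 0.857 ≈ 103 complete.
- 10% missed per visit: 0.90³ = 0.729, and 120 × 0.729 ≈ 87 complete.

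The Results section says T1 and T2 collection is complete for all participants, with 48 + 49 = 97 enrolled at that date. For those 97, loss in the named model would arise only at T3. Anyone missing T3 would then also lose observed T0, T1 and T2 values.

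**3. Possible bias (all inputs assumed).** Let p be the dropout proportion in an arm, and let dropouts improve δ SD less than completers. The completers' mean exceeds the full-arm mean by p × δ, so the arm difference is biased by (p₁ − p₂) × δ. With 15% versus 5%:
- δ = 0.5: 0.10 × 0.5 = 0.05 SD.
- δ = 1.0: 0.10 × 1.0 = 0.10 SD.

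With equal dropout and equal δ in both arms, the bias is zero.

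**4. Baseline adjustment.** Assume equal variances at each visit and correlation ρ between baseline and follow-up. In units of the outcome variance, the variance of a single-visit contrast is proportional to 2(1 − ρ) for a change score and 1 − ρ² with baseline as covariate.

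| ρ | Change score | Baseline-adjusted | Reduction |
|---|---|---|---|
| 0.3 | 1.40 | 0.91 | 35% |
| 0.5 (the plan's value) | 1.00 | 0.75 | 25% |
| 0.7 | 0.60 | 0.51 | 15% |

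At ρ = 0.5 the change score does no better than ignoring baseline, which also gives 1.00.

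**5. Is power at risk?** Take the protocol's effect size f = 0.20 and ρ = 0.5, two groups, and m = 4 measurements (T0 to T3). The interaction test has noncentrality λ = f² × N × m / (1 − ρ), with 3 and 3(N − 2) degrees of freedom. At N = 108, λ = 0.04 × 108 × 4 / 0.5 = 34.56 and power is 0.9995. At 96 and 84 completers it is 0.9985 and 0.9955. On the protocol's own inputs, losing completers does not threaten power.

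**6. Strata.** Omitting university and gender from the model leaves the estimated arm difference unbiased. To the extent that they predict outcome, it makes the standard errors too large. The documents give no figure from which to size this.

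**The case against.** The strongest reply is that the article nowhere says complete cases only. Repeated measures ANOVA can serve an intention-to-treat analysis if missing values are imputed, and handling of missing data is commonly left to an analysis plan, which is not shown. That stands as far as it goes: such a document could repair the conflict. But it would have to add to, or replace, the method that the article names. The point is that a stated method does not fit a stated population; it is not a complaint about omitted detail.

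Several stronger readings are tempting and are not supported:
- A reader might put the completers at 98 of 120, from 0.95⁴ = 0.815. That counts four follow-ups, whereas the named ANOVA stops at T3, and the Results section reports T1 and T2 complete for those enrolled.
- A reader might infer that the main result will be biased. The protocol gives no dropout by arm and no outcome difference for dropouts. It mentions sleepiness and reduced vigilance, not dropout.
- A reader might treat the omitted strata and unadjusted baseline as errors of validity. Under randomisation, the group-by-time test remains valid without them. Baseline is used, though inefficiently, and the wording on class year and gender is not an exhaustive list.
- A reader might expect a loss of power. The check above shows none on the protocol's inputs.

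It is also fair to say that a mixed model is not a complete cure. A participant with no post-baseline value still contributes nothing to it, and bias remains if dropout depends on values that were not observed.

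**Conclusion.** The point holds in two parts of unequal weight. The main part is the mismatch between including all participants and a method that conventionally excludes anyone with a missed visit. Its firm size is about 12 of 120 students at the protocol's own 10% dropout. Any bias is of unknown size, and the range of 0.05 to 0.10 SD is illustrative only.

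The second part concerns efficiency. Neither stratification factor is in the efficacy model, and baseline is not a covariate. At the plan's correlation, adjusting for baseline would cut the variance of a single-visit contrast by 25%, or by 15% to 35% for correlations of 0.7 to 0.3. This assumes equal variances across visits. The gain from the strata cannot be sized.

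**What to change.** Replace the ANOVA with a linear mixed model for repeated measures (SPSS MIXED) on all available post-baseline data. Use arm, visit, arm × visit, baseline score, university and gender as fixed effects, with unstructured covariance. Analyse participants in the arm to which they were randomised. Report the adjusted arm difference at each visit named in the hypotheses (T2, T3 and T4). Data Analysis stops at T3 although Assessment Points runs to T4, so the visit list needs to be aligned in the same edit.

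State the missing-at-random assumption. Say how any participant with no post-baseline value is accounted for, for example by a sensitivity analysis. The separate class-year and gender regressions can stay if they are labelled descriptive.

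The cost is a revised paragraph and different syntax in the same software, with no new data. Record the change before the outcomes are analysed, since the Blinding section says that the analyst has access to all data.

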**Methods:**

A parallel group, RCT with a target sample of 120 medical students recruited from government-based medical universities in Malaysia. Eligible participants will be randomized to internet group CBT-I or internet group SHE in a 1:1 ratio. Assessments will be performed at baseline, post-intervention, 1 month, 3-months, and 6-months. The primary outcome is between-group differences in sleep quality and executive function post-baseline. The secondary outcomes include pre-sleep worry, attitude about sleep, sleep hygiene and sleep parameters.

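### The follow-up to the ANOVA is paired t tests within each arm and effect sizes for undefined trends, which cannot test or estimate the between-arm differences the hypotheses name

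*Protocol article*

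**What the plan says.** The question is between arms. The Abstract (Methods) states: "The primary outcome is between-group differences in sleep quality and executive function post-baseline". Under Research Aim and Hypotheses, the first hypothesis reads "ICBT-I will lead to a significant improvement in SQ compared with the SHE intervention at 1 month (T2), 3 months (T3), and 6 months (T4)", and the second and third take the same form for executive function and the sleep parameters.

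The Data Analysis section sets out these steps:

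- Changes from baseline at the follow-up "time points will be assessed for treatment effects using repeated measures analysis of variance".
- "Both treatment and time interaction effects will be examined". The Sample Size Estimation section sizes the trial on the within-between interaction.
- Paired-samples t "tests will then be conducted within each condition to evaluate possible simple or main effects". No condition is attached to this step.
- "Significant findings and statistical trends will be further analyzed using Cohen" d, described as an "effect size, which accounts for the correlation between pre- and posttreatment values".

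Linear regressions with class year and gender follow, and then mediation analyses for the fourth hypothesis. No contrast between arms at a named visit is described.

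**The concern.** A paired t test inside one arm asks whether that arm changed from baseline. It says nothing about whether the arms differ. When one arm reaches significance and the other does not, the pair of results is easily read as superiority, although no difference has been tested.

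This trial is exposed to that reading. The comparator is active, and the Introduction itself reports sleep hygiene education as equally effective in improving sleep quality. Entry requires a PSQI score above 5 (Data Collection Procedures), so some regression to the mean is expected in both arms. Change within an arm is therefore likely even if the treatments do not differ, and a pre-post effect size would include it.

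The word trends has no threshold. It allows results that miss the 0.05 level used in the sample size calculation to be carried forward selectively.

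**Working it through.** **What each step can answer**

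| Step in Data Analysis | Compares the arms? | Answers which visit and direction? |
|---|---|---|
| Treatment-by-time interaction | Yes | No, it is an omnibus test |
| Paired t test within each condition | No | Only for change within that arm |
| Cohen d using the pre-post correlation | Most naturally no (a pre-post effect size) | Only for change within that arm |

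The hypotheses name both a direction (ICBT-I better) and visits (T2, T3, T4). The interaction alone does not resolve these, and the step chosen to resolve them does not compare the arms.

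**Size of the risk if the paired tests are read as a comparison**

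The article gives no figure of its own for this, so there is nothing to reproduce first. Inputs:

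- n = 54 per arm: 60 per group less the stated 10% dropout, 60 × 0.9 = 54.
- Two-sided alpha of 0.05, as in Sample Size Estimation. The critical value of t on 53 degrees of freedom is 2.006.
- A common true change d in both arms, in SDs of the change score. This is an assumption; 0.3 to 0.5 is shown.

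The probability p that one arm is significant comes from the noncentral t distribution with noncentrality d√n. The arms are independent, so P(ICBT-I significant, ISHE not) = p(1 − p).

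| d | d√54 | p | p(1 − p) |
|---|---|---|---|
| 0.3 | 2.205 | 0.581 | 0.581 × 0.419 = 0.243 |
| 0.4 | 2.939 | 0.823 | 0.823 × 0.177 = 0.146 |
| 0.5 | 3.674 | 0.950 | 0.950 × 0.050 = 0.047 |

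With no true difference, a two-sided 5% between-arm test favours ICBT-I in 2.5% of trials, whatever the common change.

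**Sensitivity to n.** With 48 per arm the three values are 24.9%, 17.5% and 7.0%. With 60 per arm they are 23.4%, 11.9% and 3.1%. The risk peaks at 25%, where p = 0.5, and falls away as the common change grows: at d = 0.6 with 54 per arm it is 0.9%.

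**Effect of conditioning on the interaction.** In simulation (T0 to T3, correlation 0.5, 54 per arm, equal change), suppose the paired tests are read only after a significant interaction. Exactly one arm is then significant at a given visit in about 3.5% of trials at d = 0.3 and 1.4% at d = 0.5. The article does not state this condition.

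**Multiplicity of the replacement.** Three unadjusted between-arm contrasts on one outcome, with correlation 0.5 between them, give a familywise error of about 12.5%. Ordering the two primary outcomes while leaving the visits unadjusted would therefore not hold 5%.

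**The case against.** The strongest defence is that a between-arm test is both planned and powered. The paired tests come afterwards, for simple or main effects, which is how ANOVA follow-up is often described. The article nowhere says that superiority will be inferred by comparing significance across arms. It is also condensed, and an analysis plan may specify contrasts at each visit.

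Much of this stands, and it rules out several stronger readings that a reader might infer:

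- **That the plan has no valid between-arm test.** It has one, the interaction.
- **That the paired tests are the only further analysis.** Regression and mediation follow. The paired tests are only the pairwise follow-up.
- **That the false-claim risk is 49%.** At d = 0.3, 2p(1 − p) = 2 × 0.243 = 0.487. That counts trials where only ISHE is significant, which nobody would read as ICBT-I superiority, and it ignores the interaction.
- **That the plan carries a familywise error near 23%.** That figure belongs to six unadjusted between-arm contrasts (two outcomes by three visits), which the plan does not contain.
- **That Cohen d is certainly within-arm.** The wording points that way but does not say so.
- **That practice effects will inflate the reported dTMT effect sizes.** Executive function is not among the outcomes listed for the ANOVA and paired tests, so the text does not support this. That omission is a separate matter.

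The defence does not remove the core point. The article names particular tests and gives them an inferential purpose. It attaches no condition to them and admits undefined trends. The fault lies in what is stated, not in detail left to another document.

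**Conclusion.** The point holds in limited form. The omnibus interaction is sound, but its named pairwise follow-up does not address the hypotheses at T2, T3 and T4, and the trends wording weakens the 0.05 criterion. If the within-arm results were read as a comparison without regard to the interaction, a false impression of ICBT-I superiority at one visit would arise in about 24%, 15% or 5% of trials for a common change of 0.3, 0.4 or 0.5 SD, against 2.5%.

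Those figures rest on equal true change in both arms, 54 analysed per arm, and that misreading being made. The common change is assumed, and the risk is small if both arms improve strongly. The change should be made, but the plan's main between-arm test survives without it.

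**What to change.** In Data Analysis:

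1. Keep within-arm means and changes as description, without p values.
2. Replace the paired t tests with between-arm contrasts of change (ICBT-I minus ISHE) from the repeated-measures model at T2, T3 and T4. Give each a 95% confidence interval and a between-arm standardised difference. The T4 contrast needs T4 in the model, whereas the section's ANOVA text stops at T3; that mismatch should be settled at the same time.
3. Delete the reference to statistical trends.
4. State a rule that controls error across visits as well as outcomes. One option is to open the per-visit contrasts only after a significant interaction and apply Holm over the six contrasts (2 primary outcomes × 3 visits). Another is to name one primary visit, which leaves two contrasts to adjust or to test in a declared order. Testing sleep quality before executive function is one possible order; the article presents them as joint primary outcomes, so the choice is the investigators'.

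The cost is analysis wording only, with no new data or participants. Adjusted intervals will be slightly wider, and fewer results can be claimed as significant.
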